### **8.6 Definition of the evaluation groups**

Intention-to-treat (ITT) analysis

## **9. TRIAL-SPECIFIC PREVENTIVE MEASURES AND DUTIES**

### **9.1 Trial-specific preventive measures and duties**

Trial-specific preventive measures and duties are not necessary.

### **9.2 Final examination in case of premature withdrawal from the trial**

In this case it is necessary to perform a final medical examination for the safety of the child (patient group). The following procedures will be performed:

- vital signs
- physical examination
- MFM scale, 6MWT, 10 m within 10 s walking test, muscle force of knee extension and elbow flexion using hand held dynamometry
- MRI
- Adverse events
- laboratory
- collection of study medication

## **10. DUTIES ON THE PART OF THE INVESTIGATOR**

**10.1. Study conduct**

The study will be conducted according to the protocol, GCP and the legal requirements as required by Swiss law.

All changes of protocol as well as a final report will be submitted to the Ethics Committee and Swissmedic.

**10.2 Pharmacovigilance****10.2.1. Defining Adverse Events**

An adverse event (AE) is any untoward medical occurrence in a patient during or following administration of an investigational product and which does not necessarily have a causal relationship with treatment. An AE can therefore be any unfavourable and unintended sign (including an abnormal laboratory finding), symptom, or disease temporarily associated with the use of the trial drugs, whether or not considered related to the trial drugs.

**10.2.2. Defining Serious Adverse Events (SAEs)**

A Serious Adverse Event is defined in general as an untoward (unfavourable) event, associated with trial drug or trial procedure, which:

- is fatal. Death may occur as a result of the basic disease process. Nevertheless, all deaths occurring until the last administration of the study agent must be treated as an SAE and reported as such.
- is life-threatening
- requires or prolongs hospitalisation
- results in persistent or significant disability or incapacity
- is a congenital anomaly or a birth defect, or
- may require medical or surgical intervention to prevent one of the outcomes listed above
- Any other significant clinical event, not falling into any of the criteria above, but which in the opinion of the investigator requires reporting.

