**10.2.3. Defining Suspected Unexpected Serious Adverse Reactions (SUSARs)**

All SAEs assigned by the local investigator as both suspected to be related to the trial drugs and unexpected are subject to expedited reporting. An event is unexpected when information is not

consistent with the available product information or investigator brochure, or if they add significant information on the specificity or severity of an expected reaction.

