#### **10.2.4. Reporting AEs**

AEs will be collected for all patients from screening until 30 days after the last dose of treatment with a protocol IMP.

Information about AEs, whether volunteered by the patient, discovered by the investigator questioning or detected through physical examination, laboratory test or other investigation will be collected and recorded in the study files.

If requested, details of collected AEs will be made available after completion of the study.

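### Protocol 10.2.2 makes association with drug or procedure a condition of being an SAE, so serious events judged unrelated can be left out of the SAE classification

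*Protocol*

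**What the plan says.** Four parts of section 10.2 of the protocol bear on this point.

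- **AE definition (10.2.1).** An AE is an untoward occurrence "which does not necessarily have a causal relationship with treatment". The section goes on to include any "symptom, or disease temporarily associated with the use of the trial drugs, whether or not considered related to the trial drugs".
- **SAE definition (10.2.2).** The opening sentence reads "A Serious Adverse Event is defined in general as an untoward (unfavourable) event, associated with trial drug or trial procedure, which", followed by seven criteria. The first, on fatal events, notes that death may result from the underlying disease and adds: "Nevertheless, all deaths occurring until the last administration of the study agent must be treated as an SAE and reported as such". The last admits any other significant clinical event "which in the opinion of the investigator requires reporting".
- **SUSAR definition (10.2.3, repeated in substance in 10.2.6).** "All SAEs assigned by the local investigator as both suspected to be related to the trial drugs and unexpected are subject to expedited reporting".
- **Collection and reporting (10.2.4 and 10.2.5).** "AEs will be collected for all patients from screening until 30 days after the last dose of treatment with a protocol IMP". SAEs are collected from informed consent. SAEs that result in death, and fatal or life-threatening serious adverse drug reactions, go to the ethics committee within 7 calendar days.

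Section 12.1 gives the independent monitor the task of checking whether SAEs have occurred during the study.

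**The concern.** Seriousness and causality are separate questions. The usual order is to classify an event as serious on its outcome and then to judge whether it is related. Section 10.2.2 puts the causality question into the definition of seriousness, so an attribution judgement decides whether an event is counted as an SAE.

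The trial is a placebo-controlled comparison in boys aged 6.5 to 10 years with a progressive disease, and many serious events could plausibly be put down to that disease. A count of serious events regardless of cause does not depend on each investigator's view of attribution. A count restricted to associated events does. At stake are the completeness of the SAE classification and what the monitor and, in one situation, the ethics committee get to see.

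**Working it through.** No figure in the protocol is involved, so there is nothing to recompute. The check sets the definitions side by side and runs typical events through them.

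**Do the definitions fit together?**

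1. Under 10.2.1 relatedness is irrelevant to being an AE. If an SAE is an AE with a serious outcome, relatedness should be irrelevant to being an SAE too. Under 10.2.2 it is not.
2. Under 10.2.3 a SUSAR is an SAE that is suspected to be related and also unexpected. Relatedness acts there as a later filter, which presupposes that some SAEs are unrelated. If 10.2.2 has already applied such a filter, the later one is largely redundant.
3. Under 10.2.5 SAEs are collected from consent, before any trial drug is given. In that period only a trial procedure could satisfy the clause in 10.2.2.

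**What happens to particular events?**

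| Event | Recorded as AE (10.2.4) | SAE as written | SAE without the clause | Could be a SUSAR, either way |
|---|---|---|---|---|
| Serious, judged related | yes | yes | yes | yes, if unexpected |
| Hospitalising, disabling or life-threatening, judged unrelated | yes | no | yes | no |
| Death from the disease, up to last administration | yes | yes, by the exception | yes | no |
| Death judged unrelated, within 30 days after last dose | yes | no | yes | no |

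The second and fourth rows change.

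**How far do the exceptions in 10.2.2 reach?** Of the seven criteria, only the fatal one has an explicit rule that holds whatever the cause, and that rule stops at the last administration. AE collection continues for 30 days after the last dose. A death judged unrelated in that interval is an AE but, as written, not an SAE. The 7-day report in 10.2.5 is tied to SAEs resulting in death, so it would not be triggered. The discretionary last criterion stands under the same opening sentence and depends on the investigator's opinion, so it does not reliably bring the other events back in.

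**What follows downstream?** The monitor's check in 12.1 is framed in terms of SAEs. An event not classed as an SAE can fall outside it.

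**The case against.** The strongest defence is that the word associated may be meant in time only. Section 10.2.1, just before, uses it in a non-causal sense, and the protocol's usual word for causality is related. Collection from consent and the general commitment to GCP in 10.1 point the same way. On that reading nothing conflicts. The reading is possible but weak. Section 10.2.1 says explicitly that relatedness does not matter, and 10.2.2 drops that qualification. The exception for deaths would also be largely needless if any event during treatment already qualified. At best the definition is ambiguous, and an ambiguous SAE definition still needs correcting.

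Other parts of the defence stand, and they rule out some stronger conclusions that a reader might draw:

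- **That unrelated serious events go unrecorded.** They do not. Section 10.2.4 collects all AEs and puts them in the study files, with no relatedness condition. What can be lost is their classification as serious.
- **That only associated events ever count.** Deaths up to the last administration count whatever their cause.
- **That the SUSAR step works from an incomplete base.** An event judged unrelated cannot be a SUSAR under either definition. An event suspected to be related to drug or procedure passes the clause in 10.2.2.
- **That expedited reporting is widely affected.** An unrelated non-fatal SAE has no stated expedited report in any case. The only reporting gap is the one for deaths after the last dose.
- **That the comparison between arms is biased.** The trial is double-blind, and nothing in the protocol shows that attribution would differ by arm.

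How SAEs are tabulated by arm may be left to a statistical analysis plan and is not part of this point.

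**Conclusion.** The point holds as an inconsistency in the protocol's safety definitions. Followed as written, 10.2.2 leaves two kinds of event outside the SAE classification: non-fatal serious events judged unrelated, and deaths judged unrelated between the last administration and the end of AE collection 30 days after the last dose. Both can escape the monitor's SAE check, and the deaths would also not trigger the 7-day report to the ethics committee.

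The size cannot be given as a number, because the protocol states no expected SAE rate and no expected share judged unrelated. The conclusion assumes that sites read the association clause causally. If every site read it as temporal, the inconsistency would have little practical effect. AE recording, SUSAR identification and the primary efficacy analysis are unaffected.

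**What to change.** - In 10.2.2, delete the clause that requires association with drug or procedure. Define an SAE as any untoward medical occurrence from informed consent onward that meets a seriousness criterion, regardless of relatedness. Stating this directly is safer than referring back to the AE definition, because 10.2.1 speaks of events during or after administration of the product, while 10.2.5 starts at consent.
- Reconcile the sentence on deaths in 10.2.2 with the collection window in 10.2.4, so that the two no longer end at different times.
- Leave the causality judgement to 10.2.3 and 10.2.6, where it already serves to identify SUSARs.

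The cost is a short protocol change, matching CRF wording and a few more SAE forms.

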## 4.2 Trial design

This is a randomised placebo controlled trial. We plan to enrol 40-50 ambulant DMD patients aged between 6.5 and 10 years. All actively treated patients will get a daily dose of L-citrulline of 7.5 g/d separated in three doses per day (3x 2.5 g) as well as metformin 250 mg three times a day (750 mg daily). The patients randomized to the placebo group will receive matching placebo (sachets and powder and capsule look like verum but do not contain active ingredient). Treatment is given for the period of 26 weeks. Co-medication with glucocorticoids (standard treatment of care) is allowed. At baseline as well as at the end of the study clinical measures, laboratory, and MRI measures will be performed. This includes the MFM scale; 6MWT, MFC assessment using quantitative thigh muscle MRI, and laboratory blood analysis.

[figure not shown]

Figure 3: Flow chart showing the study design with screening, randomisation, and treatment period.

|                                                                                                                                                                                    | Visit 1               | Visit 2              | Visit 3            | Visit 4                              |
|------------------------------------------------------------------------------------------------------------------------------------------------------------------------------------|-----------------------|----------------------|--------------------|--------------------------------------|
|                                                                                                                                                                                    | Screening
(Day -1) | Baseline
(week 0) | Week 13
±7 days | End of Study
(week 26)
±7 days |
| Patient Information/Informed Consent                                                                                                                                               | x                     |                      |                    |                                      |
| Inclusion/Exclusion                                                                                                                                                                | x                     | x                    |                    |                                      |

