**Visit 4 = End of Study Visit (Week 26,  $\pm 7$  days)**

During this visit the following procedures will be performed:

- vital signs
- physical examination
- MFM scale
- 6MWT
- muscle force of knee extension and elbow flexion using hand held dynamometry
- 10 m within 10 s walking test
- MRI
- Adverse events
- laboratory
- collection of study medication

Patients (or their parents) can voluntarily withdraw from the study at any time. However, the investigator should try to assess the main reason and capture this information in the CRF.

In case of screening failure due to exclusion criteria the patient can be re-screened once for this study.

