## **7.2 Follow-up observation for trial subjects with adverse reactions**

Patients with adverse reactions which have occurred in the context of the study will be followed up by the investigator up to 30 days after the last visit.

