#### **10.2.5. Reporting SAEs**

SAEs will be collected for all patients beginning with informed consent. SAEs resulting in death or Serious Adverse Drug Reaction (fatal or life-threatening) have to be reported to the EC within 7 calendar days of the PI (or his research team) being informed of the event.

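### The safety windows do not match: AEs are promised to 30 days after the last dose, no contact is scheduled after week 26, and the all-deaths rule stops at the last administration

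*Protocol*

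**What the plan says.** Five parts of the protocol bear on when safety events are observed.

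- **AE collection (10.2.4):** "AEs will be collected for all patients from screening until 30 days after the last dose of treatment with a protocol IMP". The section accepts events volunteered by the patient, found on questioning, or detected by examination or laboratory test.
- **SAE collection (10.2.5):** "SAEs will be collected for all patients beginning with informed consent". No end is given.
- **SAE definition (10.2.2):** the lead-in is "an untoward (unfavourable) event, associated with trial drug or trial procedure, which", followed by a list of criteria that starts with a fatal outcome. Under that criterion the protocol notes that death may come from the underlying disease and adds that "all deaths occurring until the last administration of the study agent must be treated as an SAE and reported as such".
- **Follow-up (7.2):** patients with adverse reactions "will be followed up by the investigator up to 30 days after the last visit". The anchor is the last visit, not the last dose.
- **Schedule (4.2, Table 2 and visit lists):** the AE row is marked at visits 2, 3 and 4. The visit 1 list has no AE item. The last entry is "Visit 4 = End of Study Visit", at week 26 ±7 days. On dosing, 4.2 states: "Treatment is given for the period of 26 weeks".

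After premature withdrawal, section 9.2 lists one final examination, which includes adverse events, and no later contact.

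**The concern.** The AE rule covers all patients for 30 days after the last dose, but the schedule gives the site no occasion to ask about those days. A site that does exactly what Table 2 lists would learn of a new event after visit 4 only if the family reported it. A final report stating collection to 30 days after the last dose would then describe a period that was not systematically observed.

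The second problem is classification. The lead-in to the SAE definition requires association with trial drug or procedure. The all-deaths sentence lifts that requirement, but its stated period ends at the last administration. In the following 30 days, while AEs of any cause are still being collected, a death judged due to the disease has no automatic SAE status. Two sites, or two readers of the same file, could classify it differently.

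The stake is the completeness and consistency of the safety record in a blinded paediatric trial. No efficacy analysis is involved.

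**Working it through.** The protocol gives no figure to reproduce. The check sets the windows side by side and counts days.

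**Windows**

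| Rule | Section | Start | End | Who |
|---|---|---|---|---|
| AE collection | 10.2.4 | screening | last dose + 30 days | all patients |
| SAE collection | 10.2.5 | informed consent | not stated | all patients |
| All deaths are SAEs, any cause | 10.2.2 | not stated | last administration | all patients |
| Follow-up | 7.2 | adverse reaction | last visit + 30 days | patients with reactions only |
| Scheduled AE capture | Table 2, visit lists | visit 2 | visit 4 (week 26 ±7 days) | all patients |

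**Start.** Consent is signed at visit 1, which is screening, so 10.2.4 and 10.2.5 begin at the same visit. The mismatch is between these two sections and Table 2, where AE capture first appears at visit 2. Screening is labelled day -1, so visit 2 can pick up what happened in between. This part is minor.

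**End.** Assume that the last dose falls on the day of visit 4. Section 4.2 gives 26 weeks of treatment and study medication is collected at visit 4, so this can occur.

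- Visit 4: 26 × 7 = day 182; with ±7 days, day 175 to 189.
- End of the AE window: 182 + 30 = day 212; range 205 to 219.
- End of the all-deaths rule: day 182; range 175 to 189.
- Days with AE collection promised and no scheduled contact: 212 − 182 = 30.
- Share of the post-baseline AE window: 30/212 = 14.2%; range 30/219 = 13.7% to 30/205 = 14.6%.

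If dosing stops d days before visit 4 (d up to 30), that visit covers d of the days and 30 − d remain. Thirty days is therefore the upper limit. The percentage is a share of calendar days. It does not measure AEs missed.

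**Deaths after the last administration, by cause**

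- Judged associated with drug or procedure: meets the lead-in and the fatal criterion of 10.2.2, which has no time limit, so it is an SAE.
- Judged not associated: fails the lead-in, and the all-deaths sentence no longer applies, so it has no automatic SAE status. The last criterion in 10.2.2 still lets the investigator report it at discretion.
- Either way it is an AE: section 10.2.1 includes occurrences "during or following administration of an investigational product" whatever the cause, and 10.2.4 collects them to 30 days after the last dose.

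**The case against.** The strongest reply is that the sections mostly fit together. The all-deaths sentence widens the SAE definition for deaths on treatment and does not narrow it afterwards. Section 10.2.4 is itself an obligation on the site. Table 2 lists visits and examinations and does not forbid other contact, volunteered reports count, and 7.2 continues follow-up past visit 4. On this view only the means of contact is unspecified.

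Much of that stands, and it rules out stronger readings that a reader might infer:

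- *Deaths count as SAEs only up to the last dose.* The text has no such limit. A later death associated with drug or procedure is still an SAE.
- *Deaths have a shorter collection window than mild AEs.* A later death is still collected as an AE, and SAE collection has no stated end, so it cannot be shown to be shorter. What stops is automatic SAE status regardless of cause.
- *The post-dose data cannot be collected.* They can, through volunteered reports or an unscheduled contact. What is missing is a scheduled means.
- *About 14% of safety information is lost.* That figure counts days, under an assumption about the last dose.

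The reply does not close the gap. Section 7.2 concerns patients already known to have a reaction, so it does not detect a first event in anyone else, and it uses a different anchor from 10.2.4. An obligation covering all patients, with no contact at which to discharge it, depends on who happens to call. The missing end in 10.2.5 and the status of unrelated late deaths remain unresolved on any reading.

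**Conclusion.** The point holds as a mismatch of windows that needs reconciling. It has three parts:

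1. AE collection is promised in all patients to 30 days after the last dose, with no scheduled contact after week 26 to elicit new events.
2. SAE collection has no stated end.
3. Deaths judged unrelated in the 30 days after the last administration have no automatic SAE status, though they remain AEs.

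The size is up to 30 calendar days per patient without a scheduled capture point, on the assumption that dosing runs to visit 4; it is less if dosing stops earlier. The protocol gives no event rates from which to estimate events missed. Deaths would be expected to be rare in ambulant boys over 26 weeks, so the practical exposure is mainly to late AEs and SAEs. The primary and secondary efficacy results are unaffected. The correction is worth making because it is specific and cheap, and because following the schedule as written would leave the promised window without systematic observation.

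**What to change.** Use one window, built from bounds the protocol already states: informed consent (10.2.5) to 30 days after the last dose (10.2.4).

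- **10.2.2:** apply that window to the all-deaths sentence in place of the last administration.
- **10.2.4 and 10.2.5:** state the same start and end in both, which gives SAE collection an end.
- **7.2:** align the follow-up period with this window, or state why it is anchored to the last visit.
- **Table 2 and visit lists:** mark AE capture at visit 1, and add one scheduled contact for every patient at the end of the window, for example a telephone call 30 days after the last dose. Make clear that it also applies after premature withdrawal (9.2).

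The telephone call is one option; any scheduled contact that covers the full 30 days would serve. The cost is an amendment of wording and one call per patient: about 42 calls at the recruitment target in 8.2, or 40 to 50 over the range in 4.2. Treatment, visits up to week 26 and the efficacy analysis are unchanged.

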**10.2.3. Defining Suspected Unexpected Serious Adverse Reactions (SUSARs)**

All SAEs assigned by the local investigator as both suspected to be related to the trial drugs and unexpected are subject to expedited reporting. An event is unexpected when information is not

consistent with the available product information or investigator brochure, or if they add significant information on the specificity or severity of an expected reaction.

